#### Health-related quality of life

2.4.9

The evaluation of the Health-Related Quality of Life (HRQoL) was conducted using two general questions from the Brazilian version of WHOQOL-Bref [62], an adapted instrument composed of 26 questions based on the original WHOQOL-100 [63]. The questionnaire assesses four domains: physical, psychological, social relationships, and environment. Participants' perceptions of their health were analyzed, considering the two weeks preceding the questionnaire completion [64].

### Biological samples

2.5

#### Saliva samples

2.5.1

By following previous studies and standard procedures, saliva will be collected in a volume of 2 mL, using sterile 15 mL Falcon® tubes made of high-quality polypropylene to prevent analyte retention or contamination that may interfere with immunoassays [65]. Collection will always take place in the morning to minimize the circadian effect observed in some of the studied markers [66]. The collected material will then be cooled to −81 °C for further analysis. Subsequently, centrifugation at 25,000 rpm for 10 min will be performed [67]. From the obtained supernatant, 500 μL will be transferred to 1.5 mL Eppendorf microtubes and stored at −80 °C without any buffer or preservative to facilitate subsequent analyses of cytokines and specific immunoglobulins for the SARS-CoV-2 virus [68].

#### Blood samples

2.5.2

Blood samples will be collected via venipuncture, while the participants are fasting, by a nurse, using appropriate tubes to obtain serum and/or plasma aliquots (minimum of 500 μL). The tubes will be centrifuged at 2500 rpm for 10 min at 4 °C to separate coagulated from non-coagulated blood [67]. The obtained aliquots will then be frozen at −80 °C until subsequent analysis and determination of serum markers. For the determination of cytokines (i.e. IL-6, IL-10, and TNF-alpha), concentrations will be measured in the previously stored serum and saliva at −80 °C using ELISA kits (R&D Bioscience, USA) [69], following the manufacturer's recommendations. To determine specific Immunoglobulins (IgA, IgM, and IgG) for the SARS-CoV-2 virus, concentrations will be measured in the serum and saliva samples using the “in-house” ELISA technique, adapted from the protocol described in previous studies [70].

### Description of interventions

2.6

The interventions will be offered for 8–10 weeks, totaling 16–20 exercise sessions, with a weekly frequency of two sessions on non-consecutive days (separated by 48 h). All activities of the behavior change and health education program (G1, HEP) and the multicomponent exercise program (MEP, G2) will be delivered by two instructors. These instructors will be trained to maintain consistency in the classes based on the components of the MEP protocol and the topics discussed in the HEP program.

#### – MEP intervention

2.6.1

The MEP programs will be conducted by exercise specialists. The guidelines of the ACSM for exercise prescription in older adults will be followed [71]. Additionally, the recommendations of the Vivi Frail Program will also be adhered to Ref. [72]. There will be a total of 36 sessions, with a frequency of 2 times per week, spanning a period of 4 months. Each session will last for 50 min, divided into three blocks. The first block, lasting 10 min, will consist of aerobic and balance exercises. The second block will focus on 30 min of neuromuscular exercises, and finally, the last 10 min will be dedicated to cool-down exercises with stretching routines. Examples of the exercises to be performed are described in Fig. 2.

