## Abstract

The EISI study protocol aims to address the low participation rate in physical exercise programs among older individuals, emphasizing its significance as a non-pharmacological therapeutic approach for overall health and increased physical activity. The objectives include implementing physical activity (PA) and educational health programs in Jequié, Bahia, Brazil, targeting the Family Health Strategy population to enhance local physical activity levels among older individuals. The study also seeks to evaluate the program's feasibility, safety, and sustainability for large-scale implementation, along with assessing its impact on immune and inflammatory response biomarkers to the SARS-CoV virus, as well as physical-functional and brain health. Participants, aged 60 or above, will be divided into two groups: multicomponent exercise (MCE) and behavioral change interventions (BCI). The study employs a mixed-method approach, utilizing a non-randomized controlled short-term pathway model for a 4–8 weeks of pilot study and 16-week intervention impact assessment. Data collection encompasses various aspects such as sociodemographic information, mental health, physical fitness, fall risk, functional capacity, anthropometric measurements, hemodynamic assessment, habitual physical activity, and health-related quality of life. Blood and saliva samples are collected for cytokine and antibody biomarker analysis related to SARS-CoV immunity. Pre- and post-intervention evaluations for both groups will be conducted, with the hypothesis that MCE will yield more favorable responses compared to BCI. The study's holistic approach, including the assessment of feasibility, safety, and sustainability, aims to contribute to achieving Sustainable Development Goals (SDG) 3 and SDG 9 b y promoting accessible and sustainable healthcare initiatives for older individuals. This research aligns with global efforts to enhance health and well-being, emphasizing the importance of regular exercise in the aging population.

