The Intervention Study Protocol in Older Health (EISI-SP) aims to implement a physical exercise program for users of the Family Health Strategy in the municipality of Jequié, Bahia, Brazil, with the purpose of increasing LPA in the local population. As a secondary objective, this program will be assessed using the RE-AIM model to determine its feasibility and sustainability for large-scale implementation. Furthermore, at the end of the program, which will span 8 weeks of intervention with a multicomponent exercise and behavioral change approaches, the impact on several metabolic, immune, functional physical fitness, psychological well-being, and mental health indicators will be evaluated.

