### Study design

2.1

The EISI-SP will be a community intervention study, using a non-randomized controlled (nRCT), and short-term pathway model lasting 8–10 weeks [37], with two arms comprised physical exercise group versus control group with lifestyle behavioral change intervention. A pre- and post-design will be employed to assess the impact of the EISI program on several physical, metabolic, cognitive, and immunological function variables in the quantitative analysis. Additionally, a mix method of qualitative-quantitative approach will be conducted to evaluate the components of the RE-AIM model. This study protocol was developed based on the SPIRIT guidelines too [38].

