### Assessments

2.4

This evaluation phase involves initiating contact with the medical staff of the Family Health Strategy (FHS) to acquire pertinent information regarding participants' medical history and current health, factors that may impact their engagement in the exercise programs. To conduct the initial assessments, a standardized data collection instrument was employed. Participants completed this instrument two weeks prior to the program's commencement and one week following its conclusion. The comprehensive data collection instrument comprised eight sections, encompassing: a) socioeconomic and demographic information; b) lifestyle habits; c) physical-functional status; d) health status questionnaire; e) mental well-being and quality of life; f) questionnaire on Covid-19 infections; g) anthropometric measurements; h) fall risk assessment; and i) feasibility and sustainability of interventions. Application of these questionnaires during this phase was carried out by a team consisting of undergraduate and postgraduate students, physical education professionals, and university professors.

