#### HEP intervention

2.6.2

Based on the “*VAMOS: Vida Ativa Melhorando a Saúde*" program, the control group of HEP received lectures on health education, physical activities, healthy eating, identifying social support for an active lifestyle, and the impacts of an active lifestyle on mental health [73]. “VAMOS” is a behavior change educational program consisting of 12 sessions (see Table 01). In the proposed intervention, a total of 4 sessions will be conducted over a period of 2 months, with 2 sessions per month every 15 days, on the same day of the week, at the same time and location HSF, lasting 60–90 min each. The 4 sessions were chosen by the intervention team for this pilot project, aiming for better adherence by having fewer lectures. The intention is that, as the project progresses, all 12 lectures on each proposed theme of the “VAMOS” content will be implemented [74].

**Table 1 tbl1:** Content characterization of the HEP program based on the theoretical sessions.

1st Meeting: Active Life style	2nd Meeting: Healthy Eating	3rd Meeting: Social Support	4th Meeting: Mental Health
• How can I incorporate physical activity into my daily routine? • What perceived barriers exist for engaging in physical activity?	• What strategies can be implemented to maintain a healthy diet? • And what are the impacts of a diet high in sodium and sugar on health?	• Which individuals in my social circle can I rely on to stay more physically active? • With whom can I share my physical activity goals to enhance my network?	• What is my perception of my mental health? • How does daily physical activity positively impact mental health?

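### The exercise programme is given two incompatible doses at the same two sessions per week: 16–20 sessions in 8–10 weeks, or 36 sessions in 4 months

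*Protocol article*

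**What the plan says.** The protocol article describes the length or dose of the intervention in several places.

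- Introduction: "at the end of the program, which will span 8 weeks of intervention with a multicomponent exercise and behavioral change approaches, the impact on several" health indicators will be evaluated.
- Section 2.1, Study design: "short-term pathway model lasting 8–10 weeks".
- Section 2.6, Description of interventions, covering both arms: "The interventions will be offered for 8–10 weeks, totaling 16–20 exercise sessions, with a weekly frequency of two sessions".
- Section 2.6.1, MEP intervention: "There will be a total of 36 sessions, with a frequency of 2 times per week, spanning a period of 4 months", at 50 minutes per session.
- Abstract: a design "for a 4–8 weeks of pilot study and 16-week intervention impact assessment".
- Section 2.6.2, HEP intervention (the health-education control): "a total of 4 sessions will be conducted over a period of 2 months, with 2 sessions per month every 15 days". It adds: "The 4 sessions were chosen by the intervention team for this pilot project".
- Section 2.8, Pilot study: four weeks with one 30-minute class per week.

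Two places fix the outcome time. Section 2.4 puts the assessments two weeks before the programme's "commencement and one week following its conclusion". Section 2.9 compares the groups on measurements at baseline and once eight weeks of intervention have been given.

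**The concern.** Sections 2.6 and 2.6.1 are adjacent, use the same weekly frequency, and give session totals that differ by about a factor of two. This is not detail left to a fuller document: the article states the dose outright, twice, and the statements cannot both be true of one programme. Two teams, each following one of the sections, would deliver materially different interventions.

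The outcome time point depends on the same figures. Section 2.4 ties the post-assessment to the end of the programme, and Section 2.9 ties the analysis to eight weeks of intervention. These coincide only if the programme lasts about eight weeks. Under the schedule in Section 2.6.1, an analysis at eight weeks would test an exercise programme less than half delivered. An analysis at programme end would make the Section 2.9 statement wrong.

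**Working it through.** **Inputs.** Frequency: 2 sessions per week (Sections 2.6 and 2.6.1). Session length: 50 minutes (Section 2.6.1; Section 2.6 gives none, so the same length is assumed for the short schedule). Durations: 8 weeks (Introduction, Section 2.9), 8–10 weeks (Sections 2.1 and 2.6), 4 months (Section 2.6.1), 16 weeks (Abstract). The Abstract gives no frequency; two per week is assumed for it.

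**Step 1: reproduce the stated totals.** Sessions = 2 × weeks.

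- Section 2.6: 2 × 8 = 16 and 2 × 10 = 20. Reproduced exactly.
- Section 2.6.1: four calendar months are 4 × 365.25 / (12 × 7) = 17.4 weeks, and 2 × 17.4 = 34.8, about 35. The stated 36 needs 36 / 2 = 18 weeks, so this is close enough to be rounding.
- Taken strictly as 16 weeks: 2 × 16 = 32.

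Each section is therefore close to consistent within itself. The conflict is between them: 36 sessions at two per week cannot fit into 8–10 weeks.

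**Step 2: size of the dose difference.** Minutes = sessions × 50.

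- Short schedule: 16 × 50 = 800; 20 × 50 = 1000.
- Long schedule: 36 × 50 = 1800 (32 × 50 = 1600 if 16 weeks is taken strictly).
- Ratios: 1800 / 1000 = 1.8 and 1800 / 800 = 2.25.

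**Step 3: does the described pilot account for either schedule?** Section 2.8 gives 4 × 1 = 4 sessions and 4 × 30 = 120 minutes. It matches neither.

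**Step 4: effect on the time point.** By the end of week 8, 2 × 8 = 16 sessions have been offered. The Section 2.4 assessment falls one week after programme end.

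| Programme | Total sessions | Offered by week 8 | Section 2.4 assessment, weeks from programme start |
|---|---|---|---|
| 8 weeks | 16 | 16/16 = 100 % | 8 + 1 = 9 |
| 10 weeks | 20 | 16/20 = 80 % | 10 + 1 = 11 |
| 16 weeks | 32 | 16/32 = 50 % | 16 + 1 = 17 |
| 18 weeks | 36 | 16/36 = 44 % | 18 + 1 = 19 |

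In the first row Sections 2.4 and 2.9 are compatible: a measurement one week after an 8-week programme still follows eight weeks of intervention. In the last two rows they are not.

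**Step 5: the control arm under the long schedule.** Two months is 8 to 8.7 weeks. A common assessment 19 weeks after programme start would fall 19 − 8.7 = 10.3 to 19 − 8 = 11 weeks after HEP ends. For a 16-week programme the gap is 17 − 8.7 = 8.3 to 17 − 8 = 9 weeks.

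**The case against.** The best defence is a two-phase reading: a short pilot followed by a longer impact study. The Abstract names a pilot and a 16-week impact assessment, Section 2.6.2 ties the four HEP sessions to a pilot project that is to be expanded later, and Fig. 1, which shows the timeline, was not available. This reading remains possible but is not established by the text. The only pilot described, in Section 2.8, has neither dose. The Introduction places the impact evaluation at the end of an 8-week programme. Sections 2.1, 2.6 and 2.6.1 carry no phase label.

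Several stronger conclusions are tempting, and the document does not support them:

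- A reader might infer that the Section 2.9 time point misses programme end in every case. Under the 8-week version it does not, and the one-week lag in Section 2.4 is then no conflict.
- A reader might count 16 weeks as a third schedule. In ordinary usage 16 weeks and 4 months are the same duration, and the Abstract states no session count. There are two schedules, a short one and a long one.
- A reader might conclude that the HEP schedule is also unsettled. Section 2.6.2 fixes it, and two months fits the 8–10 weeks of Section 2.6, whose 16–20 total refers to exercise sessions.
- A reader might infer that the two arms will be measured at different times. Section 2.9 gives both groups a common point.

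**Conclusion.** The protocol contradicts itself on the dose and duration of the tested intervention. The session totals are 16–20 against 36, a factor of 1.8 to 2.25, or 800–1000 against 1800 minutes if the 50-minute session applies throughout. The effect on the analysis is conditional. If the long schedule is intended, the eight-week point in Section 2.9 falls after 16 of 36 sessions (44 %) and conflicts with Section 2.4. If the 8-week schedule is intended, Sections 2.4 and 2.9 agree, and the errors lie in the Abstract and Section 2.6.1. The visible text does not settle which is meant, although more of it favours the short schedule. This is an internal inconsistency that must be corrected, because it concerns what is delivered and when it is measured. The conclusion rests on the written sections alone. Fig. 1 might show which schedule was intended, but it could not make both sentences true of one programme.

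**What to change.** State one MEP duration and one session total, and use them throughout. The sponsor decides which.

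- **8 weeks with 16 sessions.** This matches the 2-month HEP and the analysis in Section 2.9. Correct the Abstract and Section 2.6.1, and narrow the 8–10 week range in Sections 2.1 and 2.6. Cost: wording only.
- **The 4-month schedule.** Correct the Introduction and Sections 2.1, 2.6 and 2.9. Make the total fit the weeks: 32 sessions for 16 weeks or 36 for 18 weeks, with the Abstract in agreement. Align the 2-month HEP with it, or justify measuring HEP participants roughly 8 to 11 weeks after their programme ends. Cost: wording, plus either a longer HEP or that justification.
- **Two phases, if that is what is meant.** Label the dose and the time point of each phase, for both arms. Cost: wording only.

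In every case define one post-assessment time, counted from programme start and the same in both arms, and use it in both Section 2.4 and Section 2.9. For the 8-week option this could be one week after the programme ends, that is, nine weeks after its start.

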**Fig. 2 fig2:**
[figure not shown]
Example of exercise session of MEP applied per day, divided into time blocks.

In the first block, the exercises will be performed based on time, ranging from one to two and a half minutes of execution each. In the second block of neuromuscular exercises, three sets of exercises will be performed, stimulating basic patterns of pushing, pulling, and squatting, with repetitions ranging from 12 to 20. The rest interval will vary from 1 min to 30 s, depending on the intensity increment. To increase the load, training methods such as isometric exercises will be added at the end of each set. In the third block, stretching exercises will be performed, targeting both the upper and lower limbs, with the duration of each stretch being determined based on individual needs and goals.

#### HEP intervention

2.6.2

Based on the “*VAMOS: Vida Ativa Melhorando a Saúde*" program, the control group of HEP received lectures on health education, physical activities, healthy eating, identifying social support for an active lifestyle, and the impacts of an active lifestyle on mental health [73]. “VAMOS” is a behavior change educational program consisting of 12 sessions (see Table 01). In the proposed intervention, a total of 4 sessions will be conducted over a period of 2 months, with 2 sessions per month every 15 days, on the same day of the week, at the same time and location HSF, lasting 60–90 min each. The 4 sessions were chosen by the intervention team for this pilot project, aiming for better adherence by having fewer lectures. The intention is that, as the project progresses, all 12 lectures on each proposed theme of the “VAMOS” content will be implemented [74].

**Table 1 tbl1:** Content characterization of the HEP program based on the theoretical sessions.

1st Meeting: Active Life style	2nd Meeting: Healthy Eating	3rd Meeting: Social Support	4th Meeting: Mental Health
• How can I incorporate physical activity into my daily routine? • What perceived barriers exist for engaging in physical activity?	• What strategies can be implemented to maintain a healthy diet? • And what are the impacts of a diet high in sodium and sugar on health?	• Which individuals in my social circle can I rely on to stay more physically active? • With whom can I share my physical activity goals to enhance my network?	• What is my perception of my mental health? • How does daily physical activity positively impact mental health?

#### Exercise adherence

2.6.3

Exercise adherence to the intervention protocol will be carefully monitored by the instructors. The levels of adherence for both the HEP and MEP groups will be calculated based on the number of attended sessions, which will be used as a co-variable in secondary analysis of the exercise outcomes. In case of an absence from two consecutive classes, the instructors and research team staff will proactively motivate and encourage the participants to maintain their attendance. It is expected that either the MEP group or the HEP control group attend sessions with a frequency of less than 70 % in both intervention programs.

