**Fig. 1 fig1:**
[figure not shown]
**–** Timeline of the EISI study implementation.

A minimum sample size of 20 participants per group will be recruited, which is sufficient to detect significant changes considering a statistical effect size of p = 0.05, as established take into account previous similar study [42]. However, considering a predicted adherence rate of 70 % to the program, a minimum sample size of n = 24 for both the intervention and control groups is justified.

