### Expected results

3.1

Through the implementation of EISI-SP, we hope to achieve a significant positive impact on the health and well-being of the older community-dwelling population. EISI-SP will succeed in program implementation and achieve high adherence, evaluated by the RE-AIM model. Through the qualitative approach of focus groups, the program will be adapted and improved, considering the perceptions and needs of the elderly participants. This will result in a structured physical exercise program that is feasible, sustainable, and appealing to the elderly population registered in the Family Health Strategy of Jequié, Bahia, Brazil.

Regarding the impact on global health indicators to be evaluated, it is anticipated that the exercise program will have positive and significant effects on functional capacity, health-related quality of life, mood, and psychological well-being of the elderly participants. Additionally, the program may lead to a reduction in the incidence of chronic diseases and dependence on healthcare services, contributing to healthier aging and improved quality of life.

In relation to the Sustainable Development Goals (SDGs), the EISI program is closely related to several goals, particularly SDG 3. By promoting physical activity and behavioral change, the program aims to enhance the health and well-being of the older individuals, preventing diseases and fostering a healthy and active lifestyle. Moreover, the program may also contribute to other SDGs, such as SDG 10 - Reduced Inequalities, by promoting the participation and inclusion of the in the community, and SDG 11 - Sustainable Cities and Communities, by encouraging sustainable practices in the implementation of intervention programs. Achieving these goals in real-time, the EISI study protocol can serve as a model for other regions in Brazil and other countries, contributing to the promotion of health and well-being of the elderly worldwide.

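### The printed attendance expectation of below 70 % does not fit the 70 % used for sizing, and attendance, a post-baseline variable with no stated scale, is planned as a covariate

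*Protocol article*

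**What the plan says.** Section 2.6.3 (Exercise adherence) of the protocol article makes two statements that matter here.

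- On the expected level: "It is expected that either the MEP group or the HEP control group attend sessions with a frequency of less than 70" per cent, and it adds that this applies to both programmes.
- On use in the analysis: adherence levels for both HEP (the health education control) and MEP (the exercise programme) are calculated "based on the number of attended sessions, which will be used as a co-variable in secondary analysis of the exercise outcomes".

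Other sections bear on these.

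- The sample-size paragraph (section 2.2, after Fig. 1) reaches its final number "considering a predicted adherence rate of 70 % to the program".
- Section 3.1 (Expected results) says that "EISI-SP will succeed in program implementation and achieve high adherence", and the Discussion expects good adherence.
- Section 2.6.2 offers HEP little contact: "a total of 4 sessions will be conducted over a period of 2 months". Section 2.6 gives 16–20 exercise sessions; section 2.6.1 gives 36 for MEP.
- Section 2.9 compares the groups with a t-test or Wilcoxon test and names no covariate.

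**The concern.** There are two separate problems.

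**The expected level.** The only numerical attendance expectation in the adherence section lies below the rate used for sizing and points the opposite way from the Discussion and section 3.1. A reader cannot tell whether the team foresees poor attendance or meant to set a floor.

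**The covariate.** Attendance is not a baseline characteristic. It is produced during follow-up, partly by the programme itself: two 50-minute exercise sessions a week ask something different of participants than a lecture every 15 days. It also reflects health and motivation, which influence the outcomes. Holding it fixed in a comparison of MEP with HEP can remove the part of the effect that works through attending, and it compares people who are alike in attendance but may differ in prognosis. This trial is non-randomised, so the adjustment would add a further source of bias to a comparison already open to confounding. The scale of the covariate is also left open, and on one scale it would come close to labelling the arm.

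**Working it through.** **Step 1. The plan's own figure.** The inputs are 20 per group ("A minimum sample size of 20 participants per group will be recruited") and 70 % adherence. Dividing gives 20 / 0.70 = 28.6, so 29 per group, against the stated 24. The stated 24 equals 20 × 1.2 and corresponds to 20 / 24 = 83.3 %. It is therefore not reproduced from 70 %. That is a separate sizing matter. It is noted here only to show that the 70 % is a planning input, so the adherence section should agree with it.

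**Step 2. The statements side by side.**

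| Place | Adherence expected |
|---|---|
| 2.2, sample size | 70 % |
| 2.6.3 | below 70 %, both programmes |
| 3, Discussion | good |
| 3.1, Expected results | high |

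The 2.6.3 entry is the odd one out. Reversing its direction would bring it into line with the other three, which is why a drafting slip is the likely explanation.

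**Step 3. Overlap if the covariate is a count.** HEP cannot exceed 4. A MEP participant falls within HEP's range only by attending at most 4/16 = 25 %, 4/20 = 20 % or 4/36 = 11 % of sessions.

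**Step 4. How strongly a count tracks group.** The documents give the sessions offered and 24 per group. Assumed here: the same mean attendance p in both arms (60 % or 70 %), and a between-person SD s of the attendance proportion from 0 to 0.28. For m sessions offered:

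- mean = m·p
- variance = m·p(1−p) + m(m−1)·s²
- R² = B / (B + W), where B is the squared half-difference of the two means and W is the average of the two variances
- VIF = 1 / (1 − R²)

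Highest case (36 sessions, p = 0.7, s = 0): the means are 25.2 and 2.8, so B = 11.2² = 125.44. The variances are 7.56 and 0.84, so W = 4.20. R² = 125.44 / 129.64 = 0.968 and VIF = 30.9.

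Lowest case (16 sessions, p = 0.6, s² = 0.08, so s = 0.28): the means are 9.6 and 2.4, so B = 3.6² = 12.96. The variances are 3.84 + 19.20 = 23.04 and 0.96 + 0.96 = 1.92, so W = 12.48. R² = 12.96 / 25.44 = 0.509 and VIF = 2.04.

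Simulation with 24 per group (1,000 replicates; mean r, median VIF) agrees:

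| MEP sessions | p | s | r | VIF |
|---|---|---|---|---|
| 16 | 0.6 | 0.28 | 0.72 | 2.1 |
| 16 | 0.7 | 0 | 0.95 | 10.0 |
| 20 | 0.7 | 0.14 | 0.92 | 6.3 |
| 36 | 0.7 | 0.26 | 0.85 | 3.7 |
| 36 | 0.7 | 0 | 0.98 | 32.4 |

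The standard error of the group effect grows by √VIF at a fixed residual variance: √2.08 = 1.4 to √32.35 = 5.7 times.

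**Step 5. The same covariate as a percentage.** In the same simulations, attendance as a proportion of sessions offered has a correlation with group of about 0, because both arms were given the same mean. The collinearity is gone. The objection that the variable is post-baseline is untouched, because it does not depend on scale.

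**The case against.** Several points can fairly be made on the other side.

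- **The count is only one reading.** The word raw does not appear. A level of adherence calculated from a number of sessions could be a percentage, and the same paragraph speaks in percentages. This stands, so Step 4 is conditional.
- **A between-group model is not stated.** The covariate is confined to secondary analysis, and no group term is mentioned. A dose-response analysis within the exercise arm would fit the words. This also stands, but the section defines the covariate for both arms and nothing excludes a between-group use.
- **The two rates may be different quantities.** Section 2.6.3 concerns how often sessions are attended. The 70 % in section 2.2 inflates the number of participants and so works like a retention rate. That softens the conflict with sizing, but not the conflict with the good and high adherence expected elsewhere.

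Two stronger inferences are tempting, and the documents support neither.

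- A reader might infer that, with the inequality reversed, the RE-AIM adherence criterion would be met by failure. Section 2.6.4 lists adherence as an indicator but gives no threshold, and section 2.6.3 states an expectation, not a success rule.
- A reader might infer that the wording leaves fewer than 17 adherent participants per group. But 24 × 0.70 = 16.8 follows from section 2.2 at exactly 70 %, and low average session attendance does not fix the number of participants retained.

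**Conclusion.** Two things hold. First, the attendance sentence does not agree with the sizing assumption or with the adherence expected in the Discussion and section 3.1. It is probably a slip for a minimum target, but it must be reconciled. Second, attendance is planned as a covariate although it is post-baseline and programme-dependent. Any between-group comparison adjusted for it, including a secondary one, would not estimate the programme effect on either scale.

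The size of the collinearity is conditional. If the count is used in a between-group model, with HEP at 4 sessions and MEP at 16 to 36, the VIF is about 2 to 32. This rests on assumed mean attendance of 60–70 % and an assumed between-person SD of 0 to 0.28. With wide variation between people (SD 0.26–0.28) it is only about 2 to 4, so calling the count almost collinear with group in all cases would go too far. On a percentage scale with similar attendance in both arms it vanishes. The main comparison in section 2.9 is unadjusted and is not affected.

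**What to change.** - Correct the attendance sentence in section 2.6.3 so that it agrees with section 2.2, the Discussion and section 3.1, and say whether the figure refers to sessions attended or participants retained.
- Define adherence as the percent of sessions offered in each arm. This needs a fixed denominator, so the MEP session totals in sections 2.6 and 2.6.1 must be reconciled.
- Keep attendance out of every between-group model, secondary ones included, and compare all participants by group whatever their attendance.
- Report attendance against change only within arm, labelled as descriptive.

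The cost is small: changes of wording, no new data and no change to the main comparison. One adjusted secondary analysis becomes a within-arm description.
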